## Discussion

The primary aim of the current trial is to test whether general anesthesia with xenon significantly reduces the incidence of POD in older patients undergoing elective cardiac surgery with the use of CPB.

### Novelty

Numerous in-vitro and in-vivo studies have shown that the noble gas xenon owns neuroprotective properties [11, 52, 53]. Evidence on xenon-mediated neuroprotection in humans is, however, scarce. To the best of our knowledge, four randomized controlled trials tested the efficacy of xenon for the prevention of postoperative cognitive dysfunction (POCD). Unfortunately, these studies produced controversial results [19, 20, 54, 55], most probably owing to the inclusion of heterogenous patient populations, the diversity in types of surgery, different follow-up periods in which patients were assessed for POCD, the use of different test batteries, and – at least in part – inadequate sample sizes. Moreover, not all studies focused on patients known to exhibit a particularly high risk for the development of neurocognitive complications.

Our clinical trial will assess the efficacy of xenon for the prevention of POD in cardiac surgery. Due to its scarcity, xenon is extremely costly. These expenses will only be justified when the promising observations with xenon in preclinical experiments can be translated into a better outcome for the geriatric population. POD has been demonstrated to be associated with important short-term and long-term complications and occurs particularly frequently in patients older than 65 years. Our study will, therefore, focus on an extremely vulnerable population. We will employ well-validated methods for delirium screening and also assess long-term neurocognitive function.

### Limitations

Investigator II, who performs the xenon or sevoflurane anesthesia, cannot be blinded to the kind of intervention. However, this investigator will have to adhere to a strict hemodynamic treatment protocol in order to ensure equivalent management in both groups and avoid bias. Moreover, investigators blinded to the group affiliation will assess all postoperative outcomes of the current trial, including the primary endpoint and the majority of secondary outcomes.

Furthermore, the noble gas xenon will only be administered during the intraoperative period. This is exactly the time period in which neuronal injury leading to POD and neurocognitive deterioration is expected to occur and during which neuroprotective interventions should presumably have the greatest benefit. However, any potential advantages of xenon with respect to recovery characteristics could be masked by postoperative events or interventions in the ICU or the nursing ward.

### Benefits for the participating patients

There is no guarantee that the use of xenon, instead of standard treatment with sevoflurane alone, will provide any medical advantage to the participant.

### Safety issues

The interventional treatment will be administered to patients under advanced hemodynamic monitoring in the setting of a fully equipped cardiac surgical operation room. This enables immediate detection and treatment of adverse events. Xenon inhalation will be immediately stopped in case that the study patient will show a life-threatening deterioration. After leaving the operation room, all patients will be closely monitored by the study team for the occurrence of eventual (S)AEs during the whole postoperative period until hospital discharge. Moreover, the inclusion of each individual patient into the study is indicated in the electronic hospital information system and hence visible to all physicians and nurses involved in the care of this patient. This will facilitate reporting of (S)AEs to the principal investigator. Finally, suspected unexpected serious adverse reactions will be reported by the principal investigator to the federal health authorities.

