## Background

Postoperative delirium (POD) is frequently observed after cardiac surgery with incidences ranging from 20 to 80 % [1, 2]. It is associated with short-term complications such as an increase in mortality, morbidity, costs and length of stay, but is also associated with long-term sequelae, including the development of persistent cognitive deficits, loss of independence, and increased mortality for up to 2 years [3].

The pathophysiology of POD is complex and thought to be related to cerebral ischemia-reperfusion injury, endothelial dysfunction [4], neuroinflammation [5], neurotransmitterimbalances [6, 7] and direct neurotoxic effects of anesthetics [8]. The individual baseline risk of a patient to develop POD is determined by a variety of predisposing factors that are not possible to be modified, including age, male gender, psychiatric illness, cognitive impairment (e.g. dementia) and atherosclerotic disease [2].

POD has been suggested to be precipitated by intraoperative and postoperative triggers. In contrast to the predisposing factors, precipitating factors are amenable to modification and have thus become a target of prevention strategies. Unfortunately, the unambiguous identification of precipitating factors for POD remains notoriously difficult. Numerous elements have been described, including (but not limited to) cardiovascular surgery, use of cardiopulmonary bypass (CPB), application of anesthetics and cognitively active medication, hypotension, decreased cardiac output, hypothermia and hypoxia [9, 10].

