#### Secondary endpoints

Secondary endpoints include the duration of POD (total number of days and percentage of patients with duration of POD longer than 2 days; for patients who have POD on day 5, daily clinical assessments are continued until the symptoms resolve or until the patient is discharged), the severity of POD (assessed with the delirium severity measure based on CAM (CAM-S) [40], use of physical restraints, postoperative cognitive function as analyzed with the MMSE at postoperative day 3, day 5, the day before discharge and at 6 months post surgery, and preoperative and postoperative ADL functioning as analyzed with the Katz ADL scale at baseline and the day before discharge and at 6 months post surgery.

In addition, the administration of anti-delirium medications (such as haloperidol, anxiolytics, dexmedetomidine, etc.) and duration of sedation will be registered and compared between both groups.

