Other secondary endpoints will be:Incidence of MACCE (major adverse cardiac and cerebral events, occurring until discharge from hospital and in the first 6 postoperative months); i.e. death from any cause; perioperative myocardial infarction, requirement of surgical revisions at the coronary arteries; postoperative coronary angioplasty; and stroke. Myocardial infarction is defined as the occurrence of a new Q wave in addition to a rise of more than 10 ng ml^−1^ of troponin in the early postoperative period or any episode of chest pain with typical rise and fall of cardiac enzymes thereafterOther cerebrovascular accidents not included in MACCE (transient ischemic attacks, reversible ischemic neurologic deficit)Postoperative renal function (as assessed by serum creatinine and blood urea nitrogen (BUN) levels)Requirement for blood (product) transfusionIncidence of intraoperative awareness as detected by the use of a structured Brice questionnaire [41] that will be performed one day after ICU dischargeDuration of postoperative ICU-stay and hospital staySeverity of postoperative critical illness as indicated by the Acute Physiology and Chronic Health Evaluation (APACHE) [42] II score once within 24 hours after admission to the ICU and the Sequential Organ Failure Assessment (SOFA) score [43]Incidence of serious adverse events (SAE) and suspected unexpected serious adverse reactions not included above. According to the International Conference on Harmonization of Technical Requirements for Registration of Pharmaceuticals for Human Use (ICH), an adverse event (AE) will be defined as “any untoward medical occurrence in a patient or clinical investigation subject administered a pharmaceutical product and which does not necessarily have to have a causal relationship with this treatment.” A SAE is “any AE that is life threatening – results in death – requires patients re-hospitalization and/or prolongation of existing hospitalization – or results in patient’s disability” [44]Intraoperative hemodynamic and respiratory profileIntraoperative use of inotropic/vasoactive medication

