For the secondary outcomes, the used statistical test will depend on the type and distribution of the considered outcome. Normally distributed data (verified with the Shapiro-Wilk *W* test statistic) will be compared using an analysis of covariance (ANCOVA) with the dichotomized EuroSCORE as binary covariate. Intergroup comparisons of non-normally distributed data will be performed using the stratified version of the Mann–Whitney *U* test. Differences in proportions will be analyzed using the exact test for a stratified 2x2 table. Time-to-events (occurrence of POD) will be assessed from end of surgery until the occurrence of the POD. Patients will be censored if they do not experience POD at the time of the last follow-up. To obtain the cumulative distribution curves for the POD times, Kaplan-Meier estimates will be used and groups will be compared using the stratified log-rank test. A linear model for longitudinal measurements with an unstructured covariance matrix for the fixed points in time (i.e. a multivariate regression model using a direct likelihood approach) [48] and the dichotomized EuroSCORE as a binary covariate will be used to evaluate the evolution of laboratory markers.

The study will be powered to detect the differences in primary outcome between the sevoflurane-group and the xenon-group. Based on recent observations from our institute [49], the incidence of POD after cardiac surgery with sevoflurane-anesthesia is approximately 40 %. A comparable incidence has already been reported earlier by our group [50] and has also been observed by other investigators [3]. Using a 2-sided test for the detection of differences between proportions (with alpha = 5 % and applying a continuity correction), at least 91 patients per group (182 in total) are required to show with 80 % power a 50 % reduction in the incidence of POD. To compensate for possible drop-outs, we will include 190 patients in total. They will be randomized into both groups in a 1:1 ratio.

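### Active SAE monitoring ends at hospital discharge, although the SAE endpoint counts re-hospitalization and has no window of its own

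*Protocol article*

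**What the plan says.** All references are to the protocol article.

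- **Endpoint.** Secondary endpoints lists "Incidence of serious adverse events (SAE) and suspected unexpected serious adverse reactions not included above". No period is attached to it.
- **Definition.** The same item counts as serious an event that, among other criteria, "requires patients re-hospitalization and/or prolongation of existing hospitalization". Resulting disability also qualifies.
- **Monitoring.** Safety issues states that, after the operation, "all patients will be closely monitored by the study team for the occurrence of eventual (S)AEs during the whole postoperative period until hospital discharge". It adds that trial participation is flagged in the electronic hospital information system, so that treating staff can report events to the principal investigator. No end date is given for that second route.
- **MACCE.** This composite (death from any cause, myocardial infarction, surgical coronary revision, angioplasty, stroke) is counted as events "occurring until discharge from hospital and in the first 6 postoperative months".
- **Later contact.** Katz ADL is assessed at baseline and again "the day before discharge and at 6 months post surgery"; the MMSE is also repeated at 6 months.
- **Length of stay.** Hospital stay is itself a secondary endpoint, and the Background links POD to "an increase in mortality, morbidity, costs and length of stay".
- **Analysis.** Under Statistical analysis and sample size calculation, proportions are compared with an exact test for a stratified 2x2 table. That test makes no allowance for unequal observation time.

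**The concern.** Two statements do not fit together. One defines an endpoint that includes an event possible only after discharge. The other ends the described active search for such events at discharge. The SAE comparison would then be incomplete by its own definition, and a reader of the results could not tell whether few re-hospitalizations were reported because few occurred or because nobody asked.

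There is also a question of comparability. Counting to discharge gives each patient an observation window equal to the length of stay. If xenon reduces POD as hypothesized, and POD lengthens stay, the xenon arm would be watched for fewer days on average. Its SAE incidence could look somewhat lower even if the daily risk were the same in both arms.

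**Working it through.** **1. The plan's own main figure.** The article gives no SAE rate and no length of stay, so no stated safety figure can be reproduced. The sample size can. For 40 % vs 20 %, two-sided 5 %, 80 % power:

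n' = [1.96·√(2·0.30·0.70) + 0.8416·√(0.40·0.60 + 0.20·0.80)]² / 0.20² = (1.270 + 0.532)² / 0.04 ≈ 81.2, so 82 without correction.

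With continuity correction: n = (n'/4)·[1 + √(1 + 4/(n'·0.20))]² ≈ 20.3 × 2.116² ≈ 90.9, so 91 per group, as stated. The present point does not touch this number.

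**2. The windows side by side.**

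| Item | Window stated |
|---|---|
| POD (primary) | first 5 postoperative days |
| MACCE | to discharge, and first 6 months |
| MMSE, Katz ADL | last assessment at 6 months |
| SAE incidence (residual) | none with the endpoint; active monitoring to discharge |

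Of the criterion that joins re-hospitalization with prolonged hospitalization, the second half can be met in hospital and the first half cannot. Events after discharge that count as MACCE are covered to 6 months. What is left without active collection is the set of non-MACCE SAEs after discharge.

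**3. How large could the effect of unequal windows be?** From the plan: sevoflurane POD incidence, where "the incidence of POD after cardiac surgery with sevoflurane-anesthesia is approximately 40" %, and 20 % with xenon after the planned 50 % reduction. Assumed, because the documents do not give them: a base stay of 10 days, d = 1 to 5 extra days for a patient with POD, and a constant daily SAE hazard h = 1 to 3 %, identical in both arms.

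- Difference in mean stay = (0.40 − 0.20)·d = 0.2 days (d = 1) to 1.0 day (d = 5).
- P(any SAE by discharge) = p·[1 − exp(−h(10 + d))] + (1 − p)·[1 − exp(−10h)], where p is the POD incidence in the arm.

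Example, d = 5 and h = 0.01: 1 − exp(−0.15) = 0.1393 and 1 − exp(−0.10) = 0.0952. Sevoflurane: 0.4·0.1393 + 0.6·0.0952 = 0.1128. Xenon: 0.2·0.1393 + 0.8·0.0952 = 0.1040. Ratio 0.92.

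| d (days) | h per day | Sevoflurane | Xenon | Ratio |
|---|---|---|---|---|
| 1 | 0.01 | 0.0988 | 0.0970 | 0.982 |
| 1 | 0.03 | 0.2679 | 0.2636 | 0.984 |
| 3 | 0.01 | 0.1059 | 0.1005 | 0.949 |
| 3 | 0.03 | 0.2847 | 0.2719 | 0.955 |
| 5 | 0.01 | 0.1128 | 0.1040 | 0.922 |
| 5 | 0.03 | 0.3005 | 0.2798 | 0.931 |

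The ratio runs from about 0.98 to 0.92 with no true safety difference. With 95 patients per arm, the largest absolute gap in the table is 95 × (0.3005 − 0.2798) ≈ 2 patients. If stay is the same in both arms, or the window is fixed, the ratio is 1.00.

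**The case against.** The case for leaving the text alone has several good parts.

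- **The schedule is not visible.** Fig. 1 shows the study visits and its legend lists AE and SAE, but the figure is not available here. SAE checks at 6 months cannot be ruled out, and the article condenses a fuller protocol. This stands as a limit on what can be claimed. If such checks exist, the sentence in Safety issues is incomplete and still needs correcting.
- **There is a second reporting route.** The electronic flag may bring some re-admissions to the principal investigator. This stands too, but the route is passive, and re-admissions to other hospitals might not reach it.
- **The definition is a general one attributed to ICH.** A standard definition can contain an element outside a given collection window. That is so, but here the definition is attached to an endpoint whose window is not stated, so the reader has no means of seeing the restriction.
- **A tiered scheme is defensible.** Xenon is given only during surgery, so many related events would be expected early. Following MACCE to 6 months and other SAEs to discharge could be a deliberate choice, but the article does not say that it is.

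Stronger readings are tempting and are not supported. A reader might infer that late SAEs in general are missed; death, infarction, coronary re-intervention and stroke are counted to 6 months, and Katz ADL at 6 months partly covers function. A reader might infer that the re-hospitalization and prolongation criterion cannot operate at all; the prolongation half works in hospital. A reader might infer that the window depends on treatment; it depends on length of stay, and nothing in the article says that xenon changes stay. Finally, a stay of 10 vs 8 days would suggest a 20 % deficit in the SAE count (8/10 = 0.80), but that 2-day difference is not in the documents. Through POD alone it would require 2/0.20 = 10 extra days per patient with POD.

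**Conclusion.** The point holds as a mismatch between the SAE endpoint under Secondary endpoints and the monitoring period under Safety issues. As written, SAEs outside MACCE after discharge are not actively collected, although the endpoint's definition includes re-hospitalization, and the observation window differs between patients.

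The number of events lost cannot be estimated, because the article gives no post-discharge SAE rate. The bias from unequal windows is a possibility rather than an established fact. Under the stated assumptions it would favour the arm with the shorter stay by about 2 to 8 % in relative terms. The constant hazard matters here: if events cluster soon after surgery, the extra days at the end of a longer stay add less. Prolonged stay is also itself an SAE criterion, so stay is partly a consequence of SAEs, which the illustration ignores.

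This is a modest point about safety ascertainment, worth acting on because the remedy is cheap. The primary endpoint, its analysis and the sample size are unaffected.

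**What to change.** Reconcile the two sections by stating one fixed SAE window, counted from surgery and equal in both arms.

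- **Preferred:** ask about re-hospitalization and other SAEs, including new disability, at the 6-month contact already planned for MMSE and Katz ADL. Report in-hospital and 6-month SAE incidence separately. If Fig. 1 or the full protocol already schedules this, say so in Safety issues.
- **If collection must end at discharge:** name the endpoint in-hospital SAEs, count it over a fixed number of postoperative days, and do not claim that it captures re-hospitalization. The number of days should be short enough that few patients have left hospital before it ends; otherwise the window is again unequal.

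The cost is a few questions at an existing contact and some additional SAE forms, a modest reporting burden. No change to enrolment or to the primary analysis is needed.

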## Trial status

The enrollment period is planned over a 36-month period starting in September 2015. The end of patient enrollment is expected for October 2018. A subsequent period of 6 months is planned for the primary data evaluation and statistical analysis including the 6-month follow-up for the assessment of long-term outcome. An additional period of 3 months is planned for remaining data evaluation, statistical analysis and publication of the results.

## Abbreviations

25-OHD: 25-hydroxy vitamin D
3D-CAM: 3-minute Diagnostic Confusion Assessment Method
ADL: Katz Index of Activities of Daily Living
AE: adverse events
ALT: alanine aminotransferase
ANCOVA: analysis of covariance
APACHE II: Acute Physiology And Chronic Health Evaluation II
AST: aspartate aminotransferase
BIS: bispectral index
BUN: blood urea nitrogen
CAM: Confusion Assessment Method
CAM-S: Confusion Assessment Method Severity score
CAM-ICU: CAM adapted for the ICU
CCI: Charlson comorbidity index
COPD: chronic obstructive pulmonary disease
CO: cardiac output
CRP: C-reactive protein
CPB: cardiopulmonary bypass
CVP: central venous pressure
DOS: Delirium Observation Scale
ECG: electrocardiogram
EEG: electroencephalogram
etCO_2_: end-tidal carbon dioxide
FFP: fresh frozen plasma
FiO_2_: fraction of inspired oxygen
FWO: Research Foundation Flanders
GCP: good clinical practice
GDS: Geriatric Depression Scale
GGT: gamma-glutamyl transferase
HR: heart rate
IABP: intra-aortic balloon pump
IBP: invasive blood pressure
ICH: Technical Requirements for Registration of Pharmaceuticals for Human Use
ICDSC: Intensive Care Delirium Screening Checklist
ICU: intensive care unit
IL: interleukin
IQCODE: Informant Questionnaire on Cognitive Decline in the Elderly
IV: intravenous
MACCE: major adverse cardiac and cerebral events
MMSE: Mini-Mental State Examination
MPAP: mean pulmonary artery pressure
NMDA: N-methyl-D-aspartate
NIBP: non-invasive blood pressure
NIRS: near-infrared spectroscopy
OR: operation room
PaCO_2_: partial pressure of carbon dioxide in the blood
PC: packed cells
POCD: postoperative cognitive dysfunction
POD: postoperative delirium
rSO_2_: regional cerebral tissue oxygenation
RASS: Richmond Agitation-Sedation Scale
SaO_2_: arterial oxygen saturation
SAPS: Simplified Acute Physiology Score
SOFA: Sequential Organ Failure Assessment score
SAE: serious adverse events
SpO_2_: peripheral oxygen saturation
SSR: sample size recalculation
SvO_2_: mixed venous oxygen saturation
TCI: target-controlled infusion
TEE: transesophageal echocardiography
